## Abstract

**Background:**

School-based comprehensive sexual health education can improve adolescent health outcomes, and web-based programs are a promising approach to overcoming challenges associated with teacher-led formats by ensuring that students receive content that is consistent, unbiased, and medically accurate. However, many adolescents do not receive high-quality sexual health education and turn to the media for information about sex and relationships. Consumption of sexual media messages is related to early and risky sexual behaviors. Media literacy education (MLE) is a proven approach to adolescent sexual health promotion, yet there are no rigorously evaluated web-based MLE programs to promote sexual and relationship health among high school students.

**Methods:**

This study will test the efficacy, in a randomized controlled trial, of *Media Aware*, a web-based comprehensive sexual health promotion program for high school students that uses an MLE approach. Participants will be students in 9th and 10th grade health classes in participating schools. Randomization will take place at the school level, and data collection will take place at three time points (i.e., pretest, posttest, and 3 months follow-up). Students in the intervention classrooms will receive *Media Aware* between pretest and posttest, and students in the delayed-intervention classrooms will receive *Media Aware* after study completion (i.e., after 3 months follow-up data collection). Students in the delayed-intervention classes will receive their standard health education programming, and teachers in the delayed-intervention classes will be asked to refrain from teaching sexual health or MLE during the study timeframe. The primary outcome variables are intentions, willingness, and behaviors related to sexual health and sexual activity.

**Discussion:**

There are currently no evidence-based comprehensive sexual health programs for high school students that are web-based and use an MLE approach. *Media Aware* has the potential to be an engaging, less expensive, and effective sexual and relationship health program for high school students. *Media Aware* is unique in two important ways: (1) the web-based format reduces many of the challenges to fidelity of implementation associated with teacher-led sexual health education; and (2) the MLE approach addresses a commonly ignored influence on adolescent sexual and relationship health, namely, media.

## Background

School-based comprehensive sexual health education programs can successfully promote adolescent sexual health [1, 2]. Evidence-based programs have been shown to delay sexual debut, reduce the number of lifetime sexual partners, increase condom use during sexual activity, and reduce sexually transmitted infections (STIs), teen pregnancy, and risky sexual behaviors [1–3]. Despite these positive outcomes, sexual health programming in the USA remains inconsistent. Less than half of states require sexual health education to be taught in schools, and just 13 states require that the information taught be medically accurate [4, 5]. Many schools are not required to implement evidence-based programs, and less than half of school districts provide professional development funding for teachers to support learning how to teach sexual health education [6], which can result in inconsistent, inaccurate, and biased instruction.

The sexual health programming that is taught in secondary education seldom includes information beyond abstinence, contraception, and HIV/STIs [5]. Topics such as healthy relationships, consent, dating violence, and gender role stereotypes all play a role in shaping adolescent sexual health and should be included in comprehensive sexual education programming [7–17]. Adolescents who do not learn about healthy relationships or consent may be at increased risk for dating violence, sexual assault, and sexual abuse [18, 19]; gender role expectations can influence youth decision-making to engage in risky sexual behavior and put gender minority youth at a greater risk for poor health outcomes [9, 20]. Therefore, there is a need for comprehensive evidence-based programs for sexual and relationship health promotion among adolescents that can be implemented with fidelity in schools.

An important influence on adolescent sexual health that is often overlooked in sexual health education is media influence. Teens spend an average of 9 h a day using entertainment media [21]. They are exposed to copious amounts of sexual content, which is often inaccurate, incomplete, and unhealthy [22]. Media have been found to influence adolescent sexual attitudes, perceptions, and behaviors [23], and can even act as a “super peer” during sexual identity development [24, 25]. Exposure to sexually explicit material is linked to stricter gender role attitudes, more permissive sexual norms [26], increased support for the objectification of women, increased acceptance of violence against women, rape myths, and sexual harassment [23]. Youth exposed to sexual media are also more likely to report having had sex than youth who have little to no exposure [27, 28].

Media literacy education (MLE) has been shown to be an effective pedagogical approach to sexual and relationship health promotion. MLE aims to improve critical thinking skills so that individuals do not simply accept media messages but, instead, evaluate them for realism and accuracy. MLE has been shown to positively affect youth cognitions including their media knowledge, criticism, and attitudes [29, 30]. Youth who receive MLE are more aware that media perpetuate inaccurate sexual messages than youth who do not receive MLE [31, 32]. MLE has been shown to redress teens’ inaccurate normative beliefs about their peers, including norms about the frequency of sexual activity and abstinence [31, 33, 34]. In studies assessing MLE’s effect on health behaviors, youth receiving MLE reported higher levels of self-efficacy regarding their own sexual behavior [31, 35], increased intentions to use a condom, if they decide to have sex [32], and reductions in risky sexual behaviors [34].

Given barriers to implementing traditional sexual health education programs and the commonly narrow focus of curricula that exclude information about the important influence of media on sexual health, there is a need for a comprehensive sexual health education program that integrates education about media influence and does not rely on teacher-led instruction for delivery. In order to address the many important topics frequently omitted from traditional sexual health education programs, including media influence, and to reduce variability in the content presented across instructors, *Media Aware*, a web-based media literacy and comprehensive sexual health education program, was developed. The program is designed to teach media literacy skills, reduce risky sexual behavior among high school students, and positively affect attitudes and cognitions that promote sexual health. *Media Aware* is designed to be completed individually by students using a web-based application that is self-paced, thereby allowing students to control the pace of their own learning. The web-based nature of the program also means that the educational content is standardized for all learners and free from individual teacher bias. The main objective of this study is to evaluate both the immediate and short-term effectiveness of *Media Aware* on adolescent sexual health and media-related outcomes. The study will also help to evaluate factors associated with fidelity of implementation and adoption, including acceptance and satisfaction as reported by both teachers and students.

## Methods/design

### Aim, design, and setting

The study design is a two-arm, randomized controlled trial (intervention group and delayed-intervention group) that will be used to evaluate the effectiveness of *Media Aware*, a web-based MLE and sexual health education program designed for high school students. It is expected that approximately 16 schools, with one teacher and their 9th or 10th grade classes from each school, will participate in the study. Data will be collected from students at three time points (i.e., pretest, immediate posttest, and 3 months follow-up). Primary outcomes will include students’ sexual behaviors, intentions, and willingness to engage in sexual activities. Secondary outcomes will include attitudes and cognitions related to sexual health (e.g., rape myth acceptance). Additionally, program completion and feedback on satisfaction using the program will be collected from both teachers and intervention students. It is expected that up to 1600 students may participate in the study. This study will take place during the 2019–2020 school year. The Standard Protocol Items: Recommendations for Interventional Trials (SPIRIT) checklist is provided as Additional file 1.

#### Sample size and power calculation

Based upon a desired power of .80, a small-to-medium effect size (.40, as defined by Cohen [36]), cluster size (participating students per school) = 100, and an intraclass correlation coefficient (ICC) for school effects = .05, a power analysis (α = .05) revealed that about 15 schools are needed to participate [37]. Attrition between pretest-posttest in a small feasibility study conducted previously was very low (< 4%); this study aimed to recruit an additional school (*N* = 16) to participate to address possible attrition. The power analysis will be updated as schools are recruited to determine if any additional schools need to be recruited to achieve the desired power.

#### Internal Review Board approval

This study protocol (Version 1) was approved by the innovation Research & Training Internal Review Board (IRB) chaired by [name] [name] on April 29, 2019. The protocol was assigned IRB number 19-002-1-EFF.

### Participant characteristics

Recruitment will take place at three levels: schools, teachers, and students. Teacher participants will be health teachers from each of the participating schools. One teacher per school will be eligible to participate. Teachers must lead at least one 9th or 10th grade health class. *Media Aware* will be evaluated with 9th and 10th grade students, who are provided with parent permission and who also provide their assent, from the classes of each of the participating teachers.

### Processes

#### Schools

High schools from across the USA will be recruited for participation. If required, school district permission for conducting external research projects in the school will be obtained prior to participation. School district administrators will receive access to *Media Aware* and study questionnaires to review, if requested. Schools will be recruited through health teachers, school district administrators, or prevention specialists. Recruitment methods of communication will include health education listservs, emails, Facebook or other Internet ads, flyers at conference booths or presentations, and phone calls or word of mouth. Efforts will be made to balance inclusion of both public and private schools and urban and rural schools, and schools ranging in their socioeconomic composition. Based on the initial power analysis, approximately 16 schools are expected to participate. Schools will be eligible if they have at least one 9th or 10th grade health classroom.

#### Teachers

One teacher from each of the participating schools will be recruited for study participation. Teachers may be recruited after a school has indicated interest in the study or may be recruited directly without prior contact with the school’s administrators. Teachers will participate with up to five of their health classrooms consisting of 9th or 10th grade students. It is anticipated that if class sizes average 20 students, up to 1600 students may be recruited. Teachers will be eligible if they can teach health education to 9th or 10th grade students, can provide technology (e.g., computers or other Wi-Fi-enabled devices) to their students for use during class to complete the web-based questionnaires and course, and are proficient in English. Teachers will review and complete an informed consent form prior to participation in the study. Participating teachers will need to agree to be randomly assigned to either the intervention or the delayed-intervention group; both groups involve implementing *Media Aware* in their classrooms. Because of the potentially sensitive nature of the program content (i.e., sexual health education), teachers will need to have access to the program during the recruitment process to review the content in order to make a decision about using the program with their classes.

#### Students

Schools will implement their district policies regarding student participation in sexual health education (e.g., opt in, opt out). Parents may request to review *Media Aware* as part of the decision-making process.

It is expected that up to 1600 students in the 9th or 10th grades may be recruited to participate in this study. Project staff and/or participating teachers will introduce the study to students and distribute consent forms. Students will be eligible to participate if they are members of participating teachers’ classes, are enrolled in 9th or 10th grade, are fluent in English, and have appropriate parental permission to receive sexual health education (per district policies). Parents can receive access to study questionnaires to review, if requested, prior to making the decision to allow their child’s participation in the research study. Students and their parents will complete assent and permission forms, respectively, and affirmative parent permission and student assent must be received before study participation begins (IRB-approved assent and permission forms are available on ClinicalTrials.gov). Consent forms specify that student participant data will be accessible to project staff only, used anonymously, and will not be sold to any outside party. The forms also state that students can stop participation at any time. This study does not involve collecting biological specimens for storage.

Informed consent will be obtained in accordance with 21 Code of Federal Regulations (CFR) Part 50 and the Declaration of Helsinki before protocol-specified procedures are carried out. The protocol is also designed to meet the Health and Human Services Regulations regarding the Protection of Human Subjects 45 CFR 46 – Subpart D.

#### Protocol

Any changes to the study protocol will be submitted by the Principal Investigator (PI) to the IRB for approval and subsequently updated in the clinical trial registry. Changes that affect the study design, budget, or timeline will be made in conjunction with the PI, the research team, and the funder. After IRB approval, the PI will distribute a copy of the revised protocol to the research team (e.g., data collectors) and ensure that all research team members are aware of the revisions that have been made. Any unexpected deviations from the protocol will be documented by the research team. With respect to the Data and Safety Monitoring Plan (DSMP), the National Institutes of Health (NIH) Program Officer will be notified of any updates, and changes will not take effect without NIH approval.

#### The intervention

*Media Aware* is a web-based, comprehensive, sexual health education program for high school students that provides developmentally appropriate and medically accurate sexual health information using an MLE approach. The pairing of sexual health information and MLE allows the program to teach students how to think critically about media messages. It especially teaches them what information is frequently omitted from media messages, such as the potential consequences of sexual activity, consent, and examples of healthy relationships. *Media Aware* consists of four interactive lessons, each containing two or three smaller mini-lessons. Each overarching lesson is designed to be completed in a 45-min class period; thus, the program is designed to take a total of four standard class periods to complete. *Media Aware* was developed by a multidisciplinary team consisting of professionals in the fields of developmental psychology, media research, web applications development, multimedia design, instructional design, and adolescent sexual health. The students in the intervention group will receive access to *Media Aware* in the time period between completing the pretest and the posttest (see Fig. 1).

**Fig. 1 Fig1:**
[figure not shown]
SPIRIT figure of enrollment, interventions, and assessments

*Media Aware* contains a Teacher Dashboard designed for use by classroom teachers, so that they are able to enroll their students in the program, track student progress, send electronic permission forms (for sexual health instruction *not* research forms), and enroll parents in a demo of the program. Teachers will also have access to a web-based Teacher Training program to help them prepare to facilitate inclusive, trauma-informed, sexual health education discussions. All teachers will receive access to *Media Aware*, the Teacher Dashboard, and the Teacher Training program. Teachers will be asked to review all of the instructional materials and associated resources.

#### Delayed-intervention group

During the course of the study, students in the delayed-intervention group will receive regularly scheduled health programming, but teachers will be asked to refrain from teaching any sexual health or MLE topics. While teachers in the delayed-intervention group may receive access to *Media Aware*, the Teacher Dashboard, and the Teacher Training prior to the student pretest, they will be instructed not to provide the program to their students until after study completion (i.e., collection of student data at 3 months follow-up).

#### Randomization

Randomization will take place at the school level to avoid contamination effects. Each school and its participating classrooms will be assigned to either the intervention or the delayed-intervention group using an open label randomized controlled trial study design. Randomization may be stratified to balance groups between public or private schools, urban or rural schools, and the average socioeconomic status level of students in schools. The research team will use Excel’s random number generator function to randomize the schools to conditions. Randomization will take place after teachers provide informed consent and appropriate school approvals for conducting the study are obtained.

#### Implementation procedure

Participating teachers will receive access to the web-based Teacher Dashboard, which will give them access to *Media Aware* and a Teacher Training program. Teachers will use the dashboard to enroll participating students in *Media Aware* and keep track of their progress. They will have the option to use the other features of the dashboard (e.g., electronic parent permission to receive sexual health education), if they choose.

This study will collect data from participating students in both study arms at three time points: pretest, posttest, and at a 3 months follow-up. All classes will be visited by project staff to administer the pretest. To ensure confidentiality, students will be spread out around the classroom and will be given privacy shields to block their computer or tablet screens from view. Secret ID numbers will be used in place of names on the questionnaires and will be sealed in envelopes between data collection time points. Students will be instructed that they can skip any questions they would like and that they may withdraw from the study at any time for any reason. Pretest questionnaires will be completed using computers or other Wi-Fi-enabled devices. Paper copies of the pretest questionnaire will be provided upon request or if technical problems with the online questionnaire occur. After pretest data collection is completed, teachers in the intervention group will have students who have permission to receive sexual health education complete *Media Aware* over the course of about one week (depending upon the school’s class schedule). It is anticipated that the program could be completed in four 45-min class periods. Teachers in the delayed-intervention schools will be asked to refrain from teaching sexual health or MLE until after the 3 months follow-up data collection. Project staff will return to all classrooms to administer the posttest questionnaire to students in the intervention group after completion of the *Media Aware* program (approximately four class periods), and to students in the delayed-intervention group approximately four class periods after their pretests have been completed. At posttest, participating students in the intervention group will also provide program feedback. After program implementation, teachers in the intervention group will provide feedback on their experiences. Project staff will return to the classrooms after approximately 3 months to administer the follow-up questionnaire. After the follow-up data are collected, teachers in the delayed-intervention group can use *Media Aware* with their students. Afterward, teachers in the delayed-intervention group will also be asked to provide feedback on their experiences implementing *Media Aware* with their students. There will be no special criteria for discontinuing or modifying allocated interventions. There is no anticipated harm.

Schools will receive a $1000 incentive for participating in the study. Teachers may receive up to $250 as an incentive for participating in the study including: a $30 incentive for each class that returns more than 80% of the parent permission forms (regardless of the parent’s participation decision) and a $100 incentive for reviewing the program, Teacher Dashboard, and Teacher Training, and completing the questionnaire on their own time. Students will be given small incentives at pretest, posttest, and follow-up (i.e., earbuds, sticky notes, water bottle) worth less than $10 in total. At follow-up, students who have participated in all three data collection time points will be entered into a classroom drawing for a $50 gift card. Students will have access to *Media Aware* and teachers will have access to the Teacher Dashboard and Teacher Training until the conclusion of the 2020 spring semester.

### Measures

#### Student measures

Students will complete questionnaires at three time points: pretest, posttest, and 3 months follow-up (see Fig. 1). The student questionnaire, consisting of approximately 180 items, will contain a compilation of measures containing assessment of variables that have previously been shown to be related to sexual health outcomes (e.g., attitudes, normative beliefs, behavioral intentions, willingness), as well as self-reports of sexual behaviors. In addition, the student questionnaire will include items designed to assess students’ media-related cognitions and media literacy skills, which are related to enhanced critical processing of media messages. Demographic questions will include the student’s age, grade level, recent grade point average (GPA), socioeconomic status (i.e., whether the student qualifies for free or reduced school lunch), ethnicity, race, sex, gender, parental education level, amount of media exposure, sexual content exposure in media, and involvement in a romantic relationship.

##### Student primary outcome measures

The primary outcome measures for students are the following:
*Sexual debut (8 items)*. Participants will be asked to indicate (1 = yes; 2 = no; 3 = unsure) their sexual experience including oral, vaginal, and anal sex (e.g., Have you ever had oral sex?). We will examine change in sexual activity between time points.*Contraception and protection use (2 items)*. Skip logic will be used. Participants who indicate sexual experience will be asked on a 3-point scale (1 = yes; 2 = no; 3 = unsure) about their contraception/protection use the last time they engaged in sexual activity (e.g., Did you use a condom the last time you had sex [anal or vaginal]?).*Willingness to engage in unprotected sex (1 item)*. Participants will be asked to indicate on a 4-point Likert scale (1 = very unwilling; 2 = unwilling; 3 = willing; 4 = very willing) how willing they are to engage in unprotected sex (i.e., Imagine you were with a boyfriend/girlfriend. They want to have sex, but neither of you have any form of protection. In this situation, how willing would you be to go ahead and have sex anyway?). This measure was adapted from Gibbons et al. [38].*Willingness to have sex (1 item)*. Participants will be asked to indicate on a 4-point Likert scale (1 = very unwilling; 2 = unwilling; 3 = willing; 4 = very willing) how willing they are to have sex in a relationship context. (i.e., Imagine you were with a boyfriend/girlfriend and they say they love you. They want to have sex. In this situation, how willing would you be to have sex?). This measure was adapted from Gibbons et al. [38].*Willingness to “hook up” against own wishes (1 item)*. Participants will be asked to indicate on a 4-point Likert scale (1 = very unwilling; 2 = unwilling; 3 = willing; 4 = very willing) how willing they are to “hook up” even if they are not sure that they really want to (i.e., Imagine you were with a boyfriend/girlfriend. They want to hook up, but you are not sure that you want to. In this situation, how willing would you be to go ahead and hook up anyway?). This measure was adapted from Scull et al. [34] and Gibbons et al. [38].*Intentions to engage in sexual activity with another person (4 items)*. Participants will be asked to indicate on a 4-point Likert scale (1 = not at all likely; 2 = unlikely; 3 = likely; 4 = extremely likely) how likely they are to engage in sexual activity in the next year (e.g., How likely is it that you will have any type of sexual contact with another person [oral sex, anal sex, vaginal sex, or genital-to-genital contact] in the next year?). This measure was adapted from L’Engle et al. [39], α = .77.*Intentions to use contraception/protection (3 items)*. Participants will be asked to indicate on a 4-point Likert scale (1 = not at all likely; 2 = unlikely; 3 = likely; 4 = extremely likely) how likely they are to use contraception (e.g., If you were to have vaginal or anal sex, how likely would you be to use a condom?). This measure was adapted from Jemmott and Jemmott [40].

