#### Outcome analyses

The immediate and short-term effectiveness of *Media Aware* for improving student outcomes will be examined using intention-to-treat analyses. Hierarchical linear modeling (with random intercepts at the school/teacher level) will likely be used to account for conditional nonindependence in outcome measures at posttest and follow-up using the SAS MIXED procedure and will examine multiple observations over time. An independent statistician will conduct interim analyses after all posttests are complete, and the PI and Co-Investigator (Co-I) will have access to the interim results. Given the minimal risk of the intervention, it is not anticipated that the trial will be terminated following these interim analyses. However, if the interim analyses suggest the possibility of any adverse effects of the trial on participants, the PI and Co-I will share the findings with the IRB chair and funder to determine how to proceed and whether or not the trial should be terminated. The PI and funder would make the final decision to terminate the trial, if necessary.

The model for the mean of each outcome will likely contain level 1 fixed effects representing the influence of (1) the student’s pretest score and (2) gender and level 2 fixed effects of condition. Student variables found to be nonequivalent between groups will be included as covariates in these models. The effect sizes will be calculated by dividing the appropriate contrast parameter by the sample standard deviation of the outcome. These analyses should reveal if there is a significant improvement in students’ sexual health and media outcomes after having received the program as compared with the delayed-intervention group. Follow-up analyses or structural equation modeling may be warranted. Qualitative analyses (media deconstruction skills) will be coded by research team members who will be blinded to intervention assignment. Unblinding will not occur.

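### The protocol sets seven co-equal primary outcomes at two time points, but its only power statement fits one unadjusted test and names neither an outcome nor a time point

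*Protocol article*

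**What the plan says.** - **Primary outcomes.** Aim, design, and setting: "Primary outcomes will include students’ sexual behaviors, intentions, and willingness to engage in sexual activities". Student primary outcome measures opens with "The primary outcome measures for students are the following" and lists seven: sexual debut, contraception/protection use, three single-item willingness measures, and two intention scales. None is placed first. Contraception/protection use is asked only of students who report sexual experience.
- **Time points and models.** Outcome analyses says that immediate and short-term effectiveness "for improving student outcomes will be examined using intention-to-treat analyses". The hierarchical model is meant to "account for conditional nonindependence in outcome measures at posttest and follow-up". The section also says: "The model for the mean of each outcome will likely contain level 1 fixed effects", with the pretest score among those effects. The result is described this way: "These analyses should reveal if there is a significant improvement in students’ sexual health and media outcomes". Neither time point is called primary.
- **Power.** Sample size and power calculation takes power .80, effect .40, 100 students per school and ICC .05, and concludes: "a power analysis (α = .05) revealed that about 15 schools are needed to participate". Sixteen schools are to be recruited, and the calculation is to be updated during recruitment. No outcome or time point is attached to it.
- **Interim.** An independent statistician analyses the data after all posttests are complete, and "the PI and Co-Investigator (Co-I) will have access to the interim results".

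**The concern.** A sample size calculation refers to a particular comparison. Here it could refer to any of seven outcomes at either of two times. That leaves two possibilities. If every primary outcome is tested at .05, the 5% applies to each test but not to the primary family. If the family is held at 5%, the alpha in the power statement is no longer the one used, and about 15 schools no longer follow from its inputs. An analysis plan that is not shown could settle which applies, but it could not make the single power figure describe both.

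What is at stake is how the main result is read. With seven unranked outcomes, one significant result could be presented as the finding. Two people who lead the trial will see the posttest results at a point when follow-up may be incomplete.

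**Working it through.** **Inputs.** From Sample size and power calculation: d = .40 (SD = 1), m = 100 per school, ICC = .05, α = .05, power .80, 15 schools needed and 16 recruited. From Student primary outcome measures: 7 outcomes. From Outcome analyses: 2 post-baseline times. Assumed because not stated: two-sided tests and equal allocation of schools.

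**1. Reproduce the plan's figure.** Variance of a school mean = ICC + (1 − ICC)/m = .05 + .95/100 = .0595. With J schools, noncentrality λ = J·d²/(4 × .0595), and the test is F with 1 and J − 2 df.

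| Schools J | λ | Power at α = .05 |
|---|---|---|
| 14 | 9.41 | .80 |
| 15 | 10.08 | .84 |
| 16 | 10.76 | .86 |

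The stated figure of about 15 is reproduced as one unadjusted two-sided test.

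**2. Family-wise error if each test is run at .05.** For k independent tests it is 1 − .95^k:

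- k = 7: 1 − .95^7 = .302
- k = 14: 1 − .95^14 = .512

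The outcomes are probably correlated, so the table below shows simulated equicorrelated normal test statistics. The correlations are assumptions.

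| Correlation | 7 tests | 14 tests |
|---|---|---|
| 0 | 30% | 51% |
| .3 | 27% | 44% |
| .5 | 23% | 35% |
| .7 | 18% | 25% |
| .9 | 11% | 14% |

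Seven tests correspond to one test per outcome, and fourteen to separate tests at posttest and at 3 months.

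**3. Marginal power per outcome if the 5% is split equally, with 16 schools.** The formula is that of step 1.

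- α = .05/7 = .00714: power .57. Reaching .80 takes 23 schools, and the effect detectable with .80 power rises from .37 to .50.
- α = .05/14 = .00357: power .45. Reaching .80 takes 26 schools, and the detectable effect is .54.

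**4. Credit the pretest covariate.** The power statement does not use it, but Outcome analyses says it will likely be in each model. If a pretest correlation r reduces variance equally at both levels, .0595 is multiplied by (1 − r²). At α = .05/7 with 16 schools:

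| Assumed r | Variance | λ | Power |
|---|---|---|---|
| 0 | .0595 | 10.76 | .57 |
| .5 | .0446 | 14.34 | .73 |
| .6 | .0381 | 16.81 | .81 |
| .7 | .0303 | 21.09 | .90 |

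So .80 for one outcome after an equal split over seven is reachable with 16 schools if r is about .6 or more. The protocol gives no value of r.

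**The case against.** The strongest reply is that this is a condensed article, and that a multiplicity procedure commonly belongs in the analysis plan, which is not shown. That stands: the absence of a procedure is not the point here. The point is what the article itself fixes, namely seven co-equal primaries and one power figure tied to none of them.

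Several stronger readings are tempting, but the text does not support them:

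- **That the protocol tests each outcome at .05.** This alpha appears only in the power calculation. Its use for each test is an inference from its being the only one given.
- **That there are at least 14 primary tests.** A mixed model over repeated observations could yield one test per outcome, hence seven. Posttest comes about four class periods after pretest, and the Discussion looks for behavioral effects over the following 3 months, so a primary test of sexual behavior at posttest is doubtful.
- **That any one significant outcome counts as success.** No such rule is written. The sentence on significant improvement also covers the media outcomes, which are secondary.
- **That the interim results are seen before follow-up is collected.** The text says only that all posttests will be complete. Schools that enrolled early may already have follow-up data.
- **That .57 is the power of the trial.** It is the marginal power for one outcome without the pretest covariate. The chance that Holm rejects at least one outcome is higher if several truly change.

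The commitment to update the power analysis during recruitment helps only if the update says which comparison it is for.

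**Conclusion.** The concern holds in this form: seven co-equal primary outcomes, examined for immediate and 3-month effects, rest on a power statement that is right for one unadjusted test and is attached to none of them. On the stated inputs, the .80 and a 5% error rate over the primary family do not hold together with 15 or 16 schools.

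If each outcome is tested at .05, the family-wise error is 11% to 30% for seven tests and 14% to 51% for fourteen, depending on assumed correlations from .9 down to 0. If 5% is split over seven, marginal power with 16 schools is about .57, or about .73 to .90 with the pretest covariate at assumed correlations of .5 to .7. The lost power may therefore be largely recoverable, but only under an assumption that the protocol does not state. All figures assume two-sided tests, equal allocation and a continuous outcome answered by about 100 students per school. Contraception/protection use does not meet the last condition, because only sexually experienced students answer it.

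This has to be settled before the interim look. Once the posttest comparisons have been seen, a choice of primary outcome or time point can no longer be shown to be independent of them.

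**What to change.** Before any posttest comparison is run, name one primary outcome that all students answer, at one time point, by protocol amendment and registry update, and attach the power statement to it. Which outcome and time is the sponsor's choice. The remaining measures become secondary.

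Alternatively, keep all seven, name one time point and test them by Holm. Then restate marginal power per outcome at the adjusted alpha (.05/7 at the first step), with the assumed pretest correlation shown, and deal separately with contraception/protection use, which has fewer respondents.

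Restricting the principal investigator's and co-investigator's access to posttest efficacy comparisons until follow-up is complete would add protection. It is optional, and reporting of possible harm would be unaffected.

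No new data are needed. The cost is either a change to the primary outcomes while enrollment is under way, which must be dated and explained, or a less favorable stated power. The planned update of the power analysis and the existing amendment route can carry either change.
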